**Fig. 3 Fig3:**
[figure not shown]
Clustered randomized trial design

#### Experimental group (training of clinicians and tools)

In the clinics allocated to the experimental group (immediate training), the clinicians who agree to participate will have access to e-TUDE for one month to complete it. Thereafter, they will receive the five C-DBs by email, at a rate of one per week for five weeks. Upon receipt of each C-DB, participants will be asked to complete the Information Assessment Measure [49]. Furthermore, each participating clinician will also be invited to use the five P-DBs with their patients. To this end, they will receive a stack of printed copies of the P-DBs for use in home care consultations and we will also leave some copies in a wall file in each consultation room of the clinic.

We will evaluate intervention fidelity using a process measure, the OPTION scale [50–52]. Based on audio-recordings of the clinical consultation, two trained observers will rate the clinicians’ level of expertise for 12 key “patient-involving” behaviors. In case of any disagreement, the observers will discuss to reach consensus.

#### Control group (usual care)

Clinicians from the clinics allocated to the control group (delayed training) will practice as usual and have access to the same training program, but after the end of data collection (Fig. 3).

#### Data collection

Clinicians from the clinics allocated to the experimental group will complete questionnaires after their training with e-TUDE and after receiving each C-DB (Table 3). These data will allow us to evaluate whether the intervention changes clinicians’ perceptions of being able to adopt shared decision-making using the novel ICanSDM scale ([name], personal communication), the role they prefer during the clinical decision-making process, and their intention to engage senior patients living with dementia and their caregivers in decision-making about a choice of health options.

**Table 3 Tab3:** Phase two (RCT) data collection steps, outcomes, processes measures, and confounding variables

Step	Outcomes (measures)
Clinician baseline, at recruitment (t0)	
Clinician, at recruitment	• Self-reported sociodemographic characteristics (confounding variables) • Self-reported interest for each of the topics addressed in the C-DB on a 1–10 visual analogue scale
Clinician, during professional training (only for those allocated to the experimental group)	
Before e-TUDE	• Role preference scale [63] • Perceptions of being able to adopt shared decision-making using the ICanSDM scale • Intention to engage senior patients living with dementia and their caregivers in decision-making about choosing a health intervention, based on the TPB [37, 38]
After e-TUDE	• Satisfaction with e-TUDE (1–5 smiley face scale) • e-TUDE usability based on the *Technology Acceptance Model* (TAM-2) [64–66]
After reception of each C-DB	• Satisfaction with DB (1–5 smiley face scale) • DB usability based on the *Technology Acceptance Model* (TAM-2) [64–66] • Value of the evidence presented in the P-DB, measured using the clinician version of the IAM [43, 67]
When training is completed	• Role preference scale [63] • Perceptions of being able to adopt shared decision-making using the ICanSDM scale • Intention to engage senior patients living with dementia and their caregivers in decision-making about choosing a health intervention, based on the TPB [37, 38]
Patient baseline, before clinical consultation (t0)	
Able patient	• Sociodemographic characteristics of the patient: self-reported by the patient (confounding variable) • Patient empowerment using the Healthcare empowerment questionnaire [47] (patient PRIMARY outcome) • Patient quality of life using the French-validated QoL-AD [50, 51] (patient outcome)
Caregiver of able patient	• Self-reported sociodemographic characteristics of the caregiver (confounding variable) • Caregiver empowerment using the Healthcare empowerment questionnaire [47] (caregiver outcome) • Caregiver burden [48, 49] (caregiver outcome) • Patient quality of life using QoL-AD [50, 51] (patient outcome)
Caregiver (and legal representative) of unable patient	• Self-reported sociodemographic characteristics of the caregiver (confounding variable). • Sociodemographic characteristics of the patient (confounding variable) • Caregiver empowerment using the Healthcare empowerment questionnaire [47] (caregiver outcome) • Caregiver burden [48, 49] (caregiver outcome) • Patient quality of life using QoL-AD [50, 51] (patient outcome)
During consultation	
Audio-recordings of the clinical consultations (OPTION-12)	• Patient involvement in decision-making, using the third-observer OPTION-12 scale [44–46] (process measure)
After clinical consultation (t1)	
Able patient	• Self-reported comfort-level with decision-making measured with the Decisional conflict scale [54, 55] (patient PRIMARY outcome) • Self-reported perceptions of the decision-making processes using the 3-item Collaborate instrument [52, 53] (process measure) • Questions about the clinical visit
Caregiver of able patient	• Self-reported comfort-level with decision-making measured with the Decisional conflict scale [54, 55] (caregiver outcome) • Self-reported perceptions of the decision-making processes using the 3-item Collaborate instrument [52, 53] (process measure) • Questions about the clinical visit
Caregiver (and legal representative) of unable patient	• Self-reported comfort-level with decision-making measured with the Decisional conflict scale [54, 55] (caregiver outcome) • Self-reported perceptions of the decision-making processes using the 3-item Collaborate instrument [52, 53] (process measure) • Questions about the clinical visit
Six months after clinical consultation (t2)	
Able patient	• Patient empowerment using the Healthcare empowerment questionnaire [47] (patient PRIMARY outcome) • Patient quality of life using the QoL-AD [50, 51] (patient outcome)
Caregiver of able patient	• Caregiver burden using a French-validated questionnaire [48, 49] (caregiver outcome) • Decisional regret [56, 57] • Patient quality of life as perceived by the caregiver QoL-AD [50, 51] (patient outcome) • Caregiver empowerment using the Healthcare empowerment questionnaire [47] (patient PRIMARY outcome)
Caregiver (and legal representative) of unable patient	• Caregiver burden using a French-validated questionnaire [48, 49] (caregiver outcome) • Decisional regret [56, 57] • Patient quality of life as perceived by the caregiver using the QoL-AD [50, 51] (patient outcome) • Caregiver empowerment using the Healthcare empowerment questionnaire [47] (patient PRIMARY outcome)

*C-DB* clinician-decision box, *P-DB* patient-decision box

After the clinicians in the experimental study group have been exposed to e-TUDE and the C-DBs, the research team will start data collection in both the control and experimental study groups. We will meet the patients/caregivers who accepted to participate at the clinic, immediately before their next consultation. They will complete the study entry questionnaires and we will assess baseline levels of patient and caregiver empowerment in healthcare (the primary outcome) [53]. We will also assess caregiver burden [54, 55] as well as patient quality of life using the QoL-AD questionnaire that will be completed by the patient, if s/he is able to do so, and by the caregiver [56, 57].

Then, participating clinicians will audio-record the discussion during the consultation and the recording will be transcribed verbatim by a professional transcriber. This will allow measuring patient/caregiver involvement in the decision-making process using the third-observer OPTION-5 scale.

Right after the consultation, we will ask patients and caregivers their perceptions of the decision-making process during the consultation using the three-item CollaboRATE instrument [58, 59] and their comfort-level with decision-making using the Decisional Conflict Scale [60, 61]. Three months after consultation, we will meet patients and caregivers at their home to ask them to complete again a questionnaire with questions about healthcare empowerment, caregiver burden [54, 55], patient quality of life [56, 57], and decisional regret [62, 63].

All data will be entered electronically in double by two research assistants, at the coordinating center (Laval University). Checks will be applied at the time of data entry into a specific field, before the data are written to the database. Data integrity will be enforced through a variety of mechanisms: referential data rules; valid values; range checks; and consistency checks against data already stored in the database. The option to choose a value from a list of valid codes and a description of what each code means will be available where applicable.

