#### Power calculation

We estimate that a sample of 162 patients will allow us to detect a mean difference of 1.476 in their empowerment in healthcare (corresponding to an effect size of 0.6) between our two groups. Assuming a standard deviation of 2.46 and an ICC (intraclass correlation coefficient) of 0.02, such a sample would give us a statistical power of 88% to detect the proposed mean difference at a significance level of 5% (Table 4). To account for an attrition and missing data rate of 10%, we have set a target of 180 patients. A previous study conducted by our research team yielded an ICC of 0.02 in a similar setting when measuring the frequency with which clinicians prescribed antibiotics after training in SDM [64]. We estimate that this convenient sample of 162 patients post intervention will allow us to detect a mean difference of 2.6% (SD = 4.8, Cohen’s D = 0.55) in decisional comfort (Decisional Conflict Scale) considering an ICC of 0.02 at a significance level of 0.05 and with a power of 80%.

**Table 4 Tab4:** Effect of study length on the power of the study

Scenario	Estimated power	Threshold of statistical significance	HCEQ Standard Deviation	Minimum detectable difference (Cohen’s effect size of 0.6)	Intra-cluster correlation	Adjusted standard deviation	Number of clusters (clinics)	Totalsample size	Study length (months)	Mean number of patients per clinic
1	0.519	0,05	2.46	1.476	0,02	2.65	6	54	1	9
2	0.76	0,05	2.46	1.476	0,02	2.85	6	108	2	18
3	0.88	0,05	2.46	1.476	0,02	2.98	6	162	3	27
4	0.92	0,05	2.46	1.476	0,02	3.21	6	216	4	36
5	0.948	0,05	2.46	1.476	0,02	3.37	6	270	5	45
6	0.963	0,05	2.46	1.476	0,02	3.53	6	324	6	54

Despite a relatively small number of clusters (six clinics to be randomized), we are confident that practice variation will be low enough to allow similar groups at baseline. Indeed, a recent systematic literature review reports rather uniform and low adoption of shared decision-making in the general practices in Canada, with two studies reporting OPTION scores of 24 ± 8 on a scale of 0–100 for one study (*n* = 152) and 19 ± 7 (*n* = 41) for the other.

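### The article disagrees with itself on which outcome is primary, and gives power for two tagged patient outcomes at an unsplit 5% each

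*Protocol article*

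**What the plan says.** Three places in Phase 2 of the protocol article bear on what is primary.

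- **Data collection, running text.** There is one primary outcome, in the singular and covering both respondents: "we will assess baseline levels of patient and caregiver empowerment in healthcare (the primary outcome". The DCS is described further on in the same section, without that status.
- **Table 3.** The patient-primary tag appears on patient HCEQ at baseline and t2 ("Patient empowerment using the Healthcare empowerment questionnaire [47] (patient PRIMARY outcome"), on a different scale at a different visit, t1 ("Self-reported comfort-level with decision-making measured with the Decisional conflict scale [54, 55] (patient PRIMARY outcome"), and on caregiver HCEQ at t2 ("Caregiver empowerment using the Healthcare empowerment questionnaire [47] (patient PRIMARY outcome"). At baseline the same caregiver measure is tagged differently: "Caregiver empowerment using the Healthcare empowerment questionnaire [47] (caregiver outcome".
- **Power calculation.** For patient HCEQ, 162 patients give 88% power at 5%. For the DCS, the same 162 give 80% power at 0.05 for a difference of 2.6 with SD 4.8. The target of 180 comes from the HCEQ calculation. Caregiver HCEQ has no stated alpha, effect or power.

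Two further details matter for the remedy. Table 3 lists patient HCEQ only in the able-patient rows; for unable patients only the caregiver completes it. Table 3 also places t2 six months after the consultation, while the Data collection text says three months.

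**The concern.** The article gives three answers to one question: a single construct in two respondents (text), three tagged measures (Table 3), and two powered patient outcomes (Power calculation). While these stand together, a favourable result on any tagged measure could be presented as the primary result, and the choice could be made after the results are known. The 5% in the power section is the error rate of one test. It is the error rate of the primary claim only if there is one primary test, or if every primary test must succeed.

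**Working it through.** **1. Reproduce the stated power.** Inputs from Power calculation and Table 4: 6 clinics, 27 patients each, 81 per arm, ICC 0.02. "Assuming a standard deviation of 2.46 and an ICC (intraclass correlation coefficient) of 0.02" applies to HCEQ, with a difference of 1.476.

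- Design effect: 1 + (27 − 1) × 0.02 = 1.52.
- HCEQ: adjusted SD = 2.46 × √1.52 = 3.03. SE = 3.03 × √(2/81) = 0.477. Difference/SE = 1.476/0.477 = 3.10. Two-sided 5% power = Φ(3.10 − 1.96) = 0.872 (0.868 with t on 160 df). With the adjusted SD of 2.98 printed in Table 4, it is 0.883 (0.880). Stated: 0.88.
- DCS: adjusted SD = 4.8 × √1.52 = 5.92. SE = 0.930. Difference/SE = 2.6/0.930 = 2.80. Power = Φ(2.80 − 1.96) = 0.798 (0.794 with t). Stated: 0.80.

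Both figures reproduce to within about a percentage point, so each calculation spends the whole two-sided 5%.

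**2. False-positive rate if any one success is enough, each test at 5%.**

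- Two tests, independent: 1 − 0.95² = 9.75%.
- Three tests, independent: 1 − 0.95³ = 14.3%.

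The documents give no correlations between outcomes. Simulation with equally correlated normal test statistics, over an assumed range, gives:

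| Assumed correlation | Two tests | Three tests |
|---|---|---|
| 0 | 9.75% | 14.3% |
| 0.3 | 9.5% | 13.6% |
| 0.5 | 9.1% | 12.5% |
| 0.7 | 8.4% | 10.9% |
| 0.9 | 7.1% | 8.3% |

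**3. If all must succeed.** The false-positive rate is at most 5%. Joint power for the two patient outcomes cannot exceed the smaller value, 80%. If they were independent it would be 0.88 × 0.80 = 70%.

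**4. Power under an equal split, same method, 162 patients.**

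| Alpha per test | HCEQ (normal / t) | DCS (normal / t) |
|---|---|---|
| 0.05 | 0.872 / 0.868 | 0.798 / 0.794 |
| 0.025 | 0.804 / 0.797 | 0.710 / 0.703 |
| 0.0167 | 0.759 / 0.750 | 0.656 / 0.647 |

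**5. Able patients.** The proportion of enrolled patients who can answer for themselves is not given. Table 4 shows how much it could matter: if 108 rather than 162 patients supplied HCEQ, its own figure is 0.76 instead of 0.88.

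**The case against.** The strongest reply is that this is a condensed article, and that test order and alpha allocation usually sit in an analysis plan, which is not shown here. That stands: the lack of a multiplicity rule is not itself the defect. It does not dispose of the point, because no such rule would make the text, Table 3 and the power section agree, and condensation does not explain two labels for one caregiver measure in one table.

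Other objections stand and limit the point:

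- A reader might infer that all three tagged outcomes are tested at a full 5%. That is documented only for patient HCEQ and the DCS.
- A reader might infer a false-positive rate of 10% or more. For the two powered outcomes 9.75% is a ceiling, and both come from the same patients, so some correlation is plausible. Exceeding 10% requires caregiver HCEQ to be a separate third test with correlation no higher than roughly 0.7. The text may instead intend patient and caregiver empowerment as one construct.
- A reader might see multiplicity growing across respondents and visits. Only three post-consultation comparisons carry the tag: caregiver DCS is a caregiver outcome, and HCEQ at t0 is a baseline value.
- The DCS did not drive the sample size. It is presented as what the 162 patients could detect.

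**Conclusion.** The contradiction about the primary outcome is real and needs settling before analysis. Its cost in error rate is conditional. If one success suffices, the rate is at most 9.75% (two tests) or 14.3% (three), and about 7 to 9.5% or 8 to 14% at assumed correlations of 0.3 to 0.9. If all must succeed there is no inflation, but the power of the primary claim is at most 80%, not 88%. The article does not say which rule applies, so it does not support a statement that the trial's error rate is inflated by a particular amount. The power figures use the article's own patient-level method; whether six clinics justify that method is a separate question and plays no part here.

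**What to change.** Before analysis:

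1. Name one primary outcome: patient-reported HCEQ at follow-up, on which the target of 180 rests. Amend the Data collection sentence, which currently includes caregivers.
2. Test the DCS at t1 at 5% only if HCEQ is significant (fixed sequence). HCEQ keeps its stated 88%. The alternative is 2.5% for each, with power restated as about 80% for HCEQ and 70–71% for the DCS.
3. Label caregiver HCEQ as a caregiver secondary outcome at both time points in Table 3 and in the text.
4. State that the primary analysis then covers able patients only. Either the 162 must all be able patients or the power must be restated.
5. Reconcile the t2 time point between Table 3 and the text; otherwise the primary outcome still has no defined time.

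The cost is relabelling and a few sentences. According to Recruitment status, recruitment was complete and Phase 2 data were being collected, so the sample size is largely settled but the hierarchy could still be declared. The downside is that the DCS can no longer carry a primary claim on its own. Under the fixed sequence its chance of a formal claim is the joint power from step 3 of the working: at most 80%, and about 70% under independence, which is much the same as under the split. Unable patients would contribute only through caregiver and secondary outcomes.

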#### Power calculation

We estimate that a sample of 162 patients will allow us to detect a mean difference of 1.476 in their empowerment in healthcare (corresponding to an effect size of 0.6) between our two groups. Assuming a standard deviation of 2.46 and an ICC (intraclass correlation coefficient) of 0.02, such a sample would give us a statistical power of 88% to detect the proposed mean difference at a significance level of 5% (Table 4). To account for an attrition and missing data rate of 10%, we have set a target of 180 patients. A previous study conducted by our research team yielded an ICC of 0.02 in a similar setting when measuring the frequency with which clinicians prescribed antibiotics after training in SDM [64]. We estimate that this convenient sample of 162 patients post intervention will allow us to detect a mean difference of 2.6% (SD = 4.8, Cohen’s D = 0.55) in decisional comfort (Decisional Conflict Scale) considering an ICC of 0.02 at a significance level of 0.05 and with a power of 80%.

**Table 4 Tab4:** Effect of study length on the power of the study

Scenario	Estimated power	Threshold of statistical significance	HCEQ Standard Deviation	Minimum detectable difference (Cohen’s effect size of 0.6)	Intra-cluster correlation	Adjusted standard deviation	Number of clusters (clinics)	Totalsample size	Study length (months)	Mean number of patients per clinic
1	0.519	0,05	2.46	1.476	0,02	2.65	6	54	1	9
2	0.76	0,05	2.46	1.476	0,02	2.85	6	108	2	18
3	0.88	0,05	2.46	1.476	0,02	2.98	6	162	3	27
4	0.92	0,05	2.46	1.476	0,02	3.21	6	216	4	36
5	0.948	0,05	2.46	1.476	0,02	3.37	6	270	5	45
6	0.963	0,05	2.46	1.476	0,02	3.53	6	324	6	54

Despite a relatively small number of clusters (six clinics to be randomized), we are confident that practice variation will be low enough to allow similar groups at baseline. Indeed, a recent systematic literature review reports rather uniform and low adoption of shared decision-making in the general practices in Canada, with two studies reporting OPTION scores of 24 ± 8 on a scale of 0–100 for one study (*n* = 152) and 19 ± 7 (*n* = 41) for the other.

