#### Data analysis

We will evaluate response rates as the number of clinics recruited divided by the number invited and the number of clinicians who agree to participate in the study divided by the number invited. We will also calculate patient recruitment rates as the number of patients recruited per attending physician per day. Audio-recordings of consultations will be collected by the research team at the end of each day and transcribed verbatim. Two trained research assistants will analyze the transcripts independently using the OPTION-5 scale [50–52] to quantify patient/caregiver involvement in the decision-making process during consultations.

We will perform descriptive statistical analyses of all the outcomes and measures. To compare the two study arms on primary and secondary outcomes, we will use hierarchical models to take into account the clustering effects of clinics and clinicians, intervention version, and repeated measures (for outcomes measured three times or more). For clinician-based outcomes, the analysis will take into account the decision considered, clinical site, sociodemographic characteristics of clinicians, and rural/urban localization of the clinic. For patient-based outcomes, the analyses will take into account clinical site, sociodemographic characteristics and dementia severity of patients, and rural/urban localization of the clinic. We will analyze all data following intention-to-treat principles. Quantitative data will be analyzed using the SAS statistical package (version 9.4).

To verify intervention fidelity, we will perform a concurrent analysis of the implementation processes (patient involvement in decision-making).

For each variable analyzed, according to the type of variable (continuous or categorical), the goodness of fit and the assumptions of each model will be assessed. We will analyze all data following intention-to-treat principles. Additionally, if the number of missing data is relatively low, then, in addition to analyzing the data by excluding missing observations, we will also perform a multiple imputation procedure on the full model and verify that results were not affected by missing information.

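### The 88% and 80% power figures use patient-level degrees of freedom; with six randomised clinics and the plan's own inputs they are about 64% and 56%.

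*Protocol article*

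**What the plan says.** The protocol article, Phase 2, Power calculation, gives the basis for the sample size. "We estimate that a sample of 162 patients will allow us to detect" the target difference, and the aim is to "detect a mean difference of 1.476 in their empowerment in healthcare (corresponding to an effect size of 0.6"). The other inputs follow: "Assuming a standard deviation of 2.46 and an ICC (intraclass correlation coefficient) of 0.02". The stated result is that "such a sample would give us a statistical power of 88% to detect the proposed mean difference at a significance level of 5" per cent. This is scenario 3 of Table 4: 6 clinics, 27 patients per clinic, adjusted SD 2.98, power 0.88. The target of 180 patients adds a 10% allowance for attrition.

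The same section claims 80% power for decisional comfort, for a difference of 2.6 with SD 4.8 and the same ICC. The ICC is taken from an earlier study that "yielded an ICC of 0.02 in a similar setting when measuring the frequency with which clinicians prescribed antibiotics after training in SDM".

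The number of clinics is acknowledged ("Despite a relatively small number of clusters (six clinics to be randomized"), but only in an argument that the arms should be similar at baseline. Under Data analysis, "we will use hierarchical models to take into account the clustering effects of clinics and clinicians". Phase 2, Study design, makes the clinic the unit of randomisation.

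**The concern.** In a cluster-randomised trial, clustering affects power in two ways. It inflates the variance of the arm difference, which the adjusted SD in Table 4 handles. It also limits how well that variance can be estimated, because the relevant replication is the number of clinics. With six clinics the second effect is large, and nothing in the power calculation allows for it.

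Two things are at stake:

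- **Reading a null result.** At 88% power, a true 0.6 SD effect would be missed about one time in eight. At 64.5% it would be missed more than one time in three. A non-significant result read against the published 88% would be taken as stronger evidence of no effect than it is.
- **Choice of test.** If the hierarchical model were tested with the large degrees of freedom that the power calculation implies, the test would reject too often under the null.

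**Working it through.** **Inputs** (Power calculation and Table 4): difference 1.476, SD 2.46, ICC 0.02, 6 clinics, m = 27 per clinic, N = 162. Assumed, because not stated: a two-sided 5% test, and three equal-sized clinics per arm (81 patients per arm).

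**1. Reproducing the plan's figures.** Adjusted SD = SD × √(1 + (m − 1) × ICC). Noncentrality = difference / (adjusted SD × √(2/n)), with n patients per arm. Power is from the noncentral t distribution with N − 2 degrees of freedom. For row 3 with the printed SD: 1.476 / (2.98 × √(2/81)) = 1.476 / 0.4683 = 3.152, and with 160 df the power is 0.880, as printed. The other rows also match:

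| Row | N | Power printed | Printed SD, N − 2 df | Formula SD, 4 df |
|---|---|---|---|---|
| 1 | 54 | 0.519 | 0.519 | 0.349 |
| 2 | 108 | 0.76 | 0.760 | 0.533 |
| 3 | 162 | 0.88 | 0.880 | 0.645 |
| 4 | 216 | 0.92 | 0.920 | 0.717 |
| 5 | 270 | 0.948 | 0.948 | 0.766 |
| 6 | 324 | 0.963 | 0.963 | 0.800 |

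Row 1 identifies the method. With 52 df the result is 0.519, the normal approximation gives 0.535, and 4 df gives 0.349. The table therefore used patient-level degrees of freedom.

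**2. Adjusted SD in row 3.** 2.46 × √(1 + 26 × 0.02) = 2.46 × √1.52 = 3.03, not 2.98. The other five rows agree with the formula (2.65, 2.85, 3.21, 3.37, 3.53). A value of 2.98 is what 162 × 0.9 / 6 = 24.3 patients per clinic would give (2.46 × √1.466 = 2.98). That origin is a guess. With 3.03 and 160 df, noncentrality is 1.476 / 0.4766 = 3.097 and power is 86.8%.

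**3. Degrees of freedom that fit the design.** Six clinics less two arm means leave 4 df, so critical t is 2.776 instead of 1.975 (160 df). With noncentrality 3.097, power is **64.5%**. Keeping the printed SD of 2.98 gives 66.0%. If all 180 enrolled patients were analysed (30 per clinic), it would be 67%.

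**4. Decisional comfort.** Adjusted SD = 4.8 × √1.52 = 5.918. Noncentrality = 2.6 / (5.918 × √(2/81)) = 2.6 / 0.9299 = 2.796. Power is 79.4% with 160 df, which matches the stated 80%, and **56.2%** with 4 df.

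**5. Detectable difference with 4 df (empowerment).** 1.79 points (0.73 SD) at 80% power and 2.02 points (0.82 SD) at 88%, against the planned 1.476 (0.6 SD).

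**6. Sensitivity to the ICC with 4 df (empowerment).** The range is assumed, since the 0.02 was observed for antibiotic prescribing and not for patient-reported empowerment.

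| ICC | Power |
|---|---|
| 0 | 81% |
| 0.01 | 72% |
| 0.02 | 64.5% |
| 0.03 | 58% |
| 0.05 | 48% |

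**7. Consequence of a large-sample test.** Balanced trials of six clinics with 27 patients each were simulated and analysed with a random-intercept model: REML, clinic variance truncated at zero, normal reference. Type I error was 6.9% at ICC 0.02 and 9.4% at ICC 0.05. Power at ICC 0.02 was about 84%. A t-test on clinic means with 4 df held about 5%.

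**The case against.** The strongest counter-argument is that 64.5% is the power of one particular analysis: an unadjusted comparison of final scores. The protocol describes a pre-post evaluation, measures empowerment at baseline, and plans to adjust for patient characteristics including dementia severity. If adjustment removed a share r² of the variance at both patient and clinic level, power with 4 df would be about 68% at r = 0.3, 76% at r = 0.5, 82% at r = 0.6 and 89% at r = 0.7. This stands as a reason to give 64.5% with its conditions attached. It does not rescue the printed figure. The protocol gives no such correlation and its calculation claims no gain from adjustment. The planned adjustment for rural or urban location is at clinic level and would use up some of the 4 degrees of freedom. Nor does baseline adjustment help decisional comfort, which is measured only after the consultation.

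Three lesser points also stand:

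- The SD slip is immaterial by itself. Essentially all of the loss comes from the degrees of freedom.
- The protocol names no degrees-of-freedom method. That may properly be left to an analysis plan, so the type I error figures are a conditional warning and not a defect found in the text.
- Recruitment is reported as complete, so the consequence now lies mainly in interpretation.

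None of this makes the published 88% and 80% correct for a trial of six randomised clinics tested at 5%.

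**Conclusion.** The concern holds. The stated power is that of a patient-level t-test with a variance inflation, and not that of a comparison of three clinics with three. On the plan's own inputs it falls from 88% to 64.5% for empowerment and from 80% to 56% for decisional comfort. No ICC from zero upward restores 88% in an unadjusted analysis. Within the six scenarios of Table 4, only the largest (324 patients) reaches 80%.

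The result rests on a two-sided 5% test, three equal clinics per arm, clinic-level degrees of freedom of 4, and no variance reduction from covariates. Unequal clinic sizes would generally lower power further. The row 3 adjusted SD is a real but minor error of about one percentage point.

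**What to change.** - Recompute Table 4 and the decisional comfort statement with 4 clinic-level degrees of freedom, and correct the row 3 adjusted SD to 3.03.
- State power as about 64% (empowerment) and 56% (decisional comfort) for an unadjusted comparison. Alternatively, state the detectable difference at 80% power, 0.73 SD (1.79 points for empowerment). In either case show a range of ICCs, for example 0.01 to 0.05. If credit is taken for baseline adjustment, give the correlation assumed and its source, and do so only for outcomes with a baseline measure.
- Specify, here or in the analysis plan, a test that matches: Kenward-Roger degrees of freedom in the hierarchical model, or a t-test on adjusted clinic means with 4 df, less any used by clinic-level covariates. Report confidence intervals on the same degrees of freedom, and read any null result from those intervals.

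The cost is a less favourable published power figure and one sentence on degrees of freedom. Enrolment, data collection and the design are unchanged.
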